
### Patient and public involvement

The study protocol underwent an external review for objective feedback prior to HREC submission. The project aims and measures were also discussed with a panel of external providers, health professionals, including an oncologist, and with a small group of cancer survivors who would not be taking part in the study.

### Statistical analyses, sample size and power calculation

Numerical data from demographic, physical and scored questionnaire outcome measures will be analysed using Excel spreadsheets, IBM©SPSS version 29 and R studio [35]. Qualitative data (mood, participant feedback survey responses, participants’ attitudes towards the intervention, enjoyment, appropriateness, suitability, convenience and perceived effectiveness of the intervention) will be analysed thematically using NVivo and following the process of Braun and Clarke (2006) [36]. Comments will be read, organised and coded using an iterative framework (familiarisation; generation of initial codes; search for themes; review of themes; definition of themes and a final report). The codes will be reviewed, discussed and refined with the coding framework drawn from the data as well as being informed by the survey questions and themes highlighted in wider literature on parkrun outcomes [19, 20]. 

Participant demographic and cancer-related variables will be summarised using descriptive statistics (e.g. count or percent; mean and standard deviation). Linear mixed effect models will be used to determine the effect of parkrun participation on the proportion of participants meeting minimal PA recommendations. These models will include a random intercept for each participant, to account for the clustering of observation on each individual (i.e. measurements at baseline, 4-weeks usual activities, following 6 months of parkrun participation, and 2-month follow-up). A histogram and quantile-quantile plot of the model residuals will be used to determine whether the assumption of normally distributed errors is met. Model fit will be assessed using the adjusted R^2^ value and the model residual standard error; the most parsimonious model will be selected for inferences. Effect sizes (Cohen’s d) will be calculated where there are significant effects of time using the pooled standard deviation as the denominator.

In the case of participant attrition from the study, or if participants miss parkrun events in the 6-month intervention period, researchers will follow up with each participant individually, either through the study or at the end of the study. Reasons for reduced attendance or attrition can be gained from the participant and this information is valuable for informing the researchers of potential barriers or issues with parkrun as a mode of cancer rehabilitation exercise.

Sample size was determined via simulation methods using a random intercept model with the R package [35]. We were interested in powering the study to detect changes in exercise adherence (measured as the proportion of cancer patients meeting minimum physical activity guidelines) and used this outcome variable in simulations. Data used to create the model were informed by previous studies [8, 10]. We assumed the average proportion of cancer patients meeting minimal physical activity guidelines for aerobic exercise was 30% [37]. Time (three levels- baseline, 6-months parkrun and follow-up), body mass index (BMI) and sex (two levels- male and female) were included as fixed factors within the sample size model. A random intercept was included for each individual participant. BMI and sex were included as fixed factors as these variables can influence exercise adherence in cancer patients [8–10]. Calculations were made assuming fixed effects of 6%, 30% and 5% for sex, time and BMI respectively, and a standard deviation of the random intercept of 2%. Based on these assumptions and a type I error rate of 5%, 80 participants give approximately 80% power to detect the specific time effect of 30% increase in the proportion of participants meeting physical activity recommendations. A minimum of 100 participants will be recruited, which even allowing for potential attrition of 20 participants would still provide a minimum sample size of 80.

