**Methods:**

This protocol describes a single-arm intervention study with participants acting as their own controls. The study accepts adults diagnosed with any type of cancer, undergoing treatment or in remission. Participants must be able to walk and have medical clearance to exercise. A sample of 100 participants will be recruited across the Sunshine Coast over two years. Data will be collected over 9-months at 4 time points: Baseline (T1); after 4-weeks of usual daily activities and cancer management prior to parkrun participation(T2); after a 6-month parkrun intervention (T3); at 2-month follow-up (T4). The primary objectives are to assess the acceptability of, and adherence to, parkrun as rehabilitation exercise. Secondary outcomes include wellness, health-related quality of life, anxiety, depression, mood, physical function, parkrun metrics, dietary intake, and diet and exercise behaviour.

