**Assessments / Tools**							
Demographics & Clinical Characteristics			X				
Physical Function (Resting HR, BP, O2sat, 6MWT, 30-s Sit-to-Stand)			X	X	X		
Health-related Quality of Life (EORTC QLQ-30) questionnaire			X	X	X	X	
Anxiety & Depression (HADS) questionnaire			X	X	X	X	
General Physical Activity (IPAQ-SF)			X	X	X	X	
Dietary Intake (MEDAS) questionnaire			X	X	X	X	
Mood (Daylio app)			X	X	X	X	
Sleep Quality (Daylio app)			X	X	X	X	
Participant Satisfaction, Diet, Exercise behaviour, Intent Feedback Surveys					X	X	
Parkrun event Adherence					X	X	
INTERVENTIONS:							
Parkrun participation					X		

This protocol describes a single group cohort study with participants acting as their own controls [23]. The study outline and timeline is shown in Fig. 1.

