### Outcome measures

*Physical function*: Resting heart rate, oxygen saturation (recorded using a pulse oximeter), resting blood pressure (standard auscultation), 6 min Walk Test (6MWT) and 30 s Sit-to-Stand test. These measures will be recorded at T1, T2 and T3. Participant rating of perceived effort (RPE) [29] will be recorded during and after the 6MWT and Sit-to-Stand test.*Quality of Life*: Assessed using the European Organization for Research and Treatment of Cancer (EORTC) Quality of Life Questionnaire (QLQ-30) [30]. This is a validated 30-question instrument used to assess different aspects contributing to HRQoL in cancer patients. Responses will be recorded at T1-T4.*Anxiety and depression*: Measured with the Hospital Anxiety and Depression Scale (HADS) [31]. This validated questionnaire consists of seven questions scoring levels of anxiety and seven assessing levels of depression. The scale takes approximately three to five minutes to complete and will be used at T1-T4.*GENERAL physical activity*: General physical and incidental activity, including ADL, and sitting time, will be assessed using the validated Short Form International Physical Activity Questionnaire (IPAQ-SF) [32] at T1-T4.*Dietary intake*: The Mediterranean Diet Adherence Screener (MEDAS) [33, 34] is a validated dietary assessment tool to determine adherence to a Mediterranean diet, which has been associated with improved health outcomes of cancer survivors. It consists of 14 questions (yes/no response) to assess the frequency of food groups included in the Mediterranean diet and will be administered at T1-T4.*Mood and sleep*: The Daylio Mood Diary basic version app is freely available for download to phone or smartwatch. The app allows daily diary entries for mood and sleep quality, and produces weekly and monthly graphs to track diary inputs. The app also allows participants to tap on icons that may contribute to mood and sleep quality e.g. food and water intake, stress, hobbies and leisure pursuits. These may contribute to parkrun adherence. Monthly graphs will be exported to the research team’s contact email by each participant, and data collated for each time point (T1-T4).*Participation satisfaction, diet and exercise behaviour, and intent*: A participant survey will be administered at T3 and T4. This consists of a checklist about eating and exercise behaviours, and participant feedback about the parkrun project during the study and 2-month follow up, including intent to change behaviours. The survey also includes a series of open-ended questions about parkrun where participants are encouraged to provide their opinions, likes and dislikes, levels of enjoyment, barriers to involvement, whether the intervention provided benefits and social support, and intention to continue with parkrun or other physical activity. For example, specific questions ask whether participants find parkrun fun and acceptable as rehabilitation exercise; whether it is easy to join in; did they meet new people (including other cancer survivors) and make new social connections; if they feel supported and incentivised to keep coming; if they feel safe participating; and is their quality of life improved.*Attendance and adherence*: Parkrun can provide the number of events attended by each participant through their national database, using the individual’s ID barcode number. Adherence will be calculated by dividing the number of events attended by each person by the number of available events in the 6-month period of the intervention and multiplying by 100 to give a percentage. If a participant does not finish an event, their time is not recorded.

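### Mood diary data are assigned to thematic coding of comments, which gives no estimate of change, and the scheduled T1 mood and sleep values cannot come from a monthly graph

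*Protocol article*

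**What the plan says.** The abstract of the protocol article names mood among the secondary outcomes: "Secondary outcomes include wellness, health-related quality of life, anxiety, depression, mood, physical function".

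Under Outcome measures, the only source given for mood is a phone diary app, which also records sleep quality: "The app allows daily diary entries for mood and sleep quality, and produces weekly and monthly graphs to track diary inputs". The material that reaches the team is stated as "Monthly graphs will be exported", with "data collated for each time point (T1-T4"). Table 1 has a row "Mood (Daylio app") and a matching row for sleep quality, each marked at T1, T2, T3 and T4.

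The section on statistical analyses, sample size and power calculation divides the data in two:

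- Numerical: "Numerical data from demographic, physical and scored questionnaire outcome measures will be analysed using Excel spreadsheets" and two statistical packages.
- Thematic: a list that opens with "Qualitative data (mood, participant feedback survey responses", handled in NVivo. The procedure is described as "Comments will be read, organised and coded using an iterative framework".

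Study objectives places T1 at enrolment and initial screening, and Table 1 gives it time 0. The Intervention section describes the first month, before parkrun, as the period that establishes baseline values.

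**The concern.** The method named for mood does not match the form in which mood is collected. Diary entries that an app can plot over weeks and months are a repeated measure. Coding comments into themes can describe what people wrote, but it cannot say whether mood was better during parkrun than before it, or by how much. The protocol makes this assignment expressly, so an analysis plan that follows it would carry the mismatch forward.

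The second problem is timing. If the diary value for a visit is drawn from a monthly graph, a visit at enrolment has no month to draw on. In a study where participants act as their own controls, the baseline has to be unambiguous. Left as it is, T1 could be left blank, filled with a single day's entry, or filled with the same month that serves T2. These give three different baselines, and the choice could vary between participants.

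**Working it through.** The plan states no figure for mood. The sample size of 80 (100 with attrition) concerns the proportion meeting physical activity guidelines. The check is therefore a comparison of the text, plus timeline arithmetic.

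**Form of the data against the method**

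| Item | Form described under Outcome measures | Analysis named in the statistical section |
|---|---|---|
| HADS, QLQ-30, MEDAS | scored questionnaires | numerical |
| Resting measures, 6MWT, sit-to-stand | physical measures | numerical |
| T3 and T4 survey, open-ended questions | free text | thematic |
| Mood | daily app entries, exported as monthly graphs | thematic |
| Sleep quality | same app, same export | not named |

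Mood is the one item whose described form and named method disagree. The mood and sleep paragraph mentions entries, icons to tap and graphs, but no written comments. The open-ended questions belong to the separate survey at T3 and T4. The diary is not a demographic or physical measure, nor a scored questionnaire, so the numerical sentence does not cover it.

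**Diary time available at each scheduled point**

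Inputs: T1 = day 0 (Table 1); 4 weeks to T2; 6 months of parkrun to T3; 2 months to T4. Assumptions: the diary starts at enrolment, since no earlier use is described; 6 months is about 180 days and 2 months about 60; entries are made every day, which makes the counts upper limits.

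- T1: 0 days, so no monthly graph.
- T2: 4 × 7 = 28 days, one pre-parkrun month.
- T3: 28 + 180 = about 208 days.
- T4: 208 + 60 = about 268 days.

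Scheduled diary points before parkrun: 2 (T1 and T2). Diary months available before parkrun: 1 (T1 to T2). One of the four scheduled points therefore cannot come from a monthly graph.

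**What remains possible**

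The T1 to T2 month lies wholly before parkrun. It can be compared with the parkrun period (up to about 180 days) and with follow-up (up to about 60 days), provided the entries are analysed numerically. The obstacle to estimating change is the assigned method. The empty T1 cell does not remove the baseline.

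**The case against.** The strongest case on the other side has four parts.

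- *The data can show change.* A reader might infer that the mood outcome is incapable of showing any change. The documents do not support that. The first month is meant to establish baseline values and yields a complete pre-parkrun graph. This objection stands: the fault lies in the named analysis, and the data remain usable.
- *T1 need not be empty.* The article does not define how data are collated for a time point, so a T1 mark might mean the first entry or the start of the diary. It would therefore be too strong to say that nothing at all can exist at T1. What remains is that a monthly graph, the only export described, cannot exist there, and the mark needs a definition.
- *Sleep is an omission only.* The statistical section says nothing wrong about sleep, and a condensed article may leave it to a fuller document. This stands. Sleep belongs in the fix because it shares the app, export and T1 mark, but the lack of a named analysis for it is no separate fault.
- *Little depends on the diary.* The primary objectives are acceptability and adherence, the hypotheses name mental health without naming mood, and HADS is scored at T1 to T4. A reader might infer that the mental-health hypothesis goes untested, but HADS prevents that. This limits the consequence but does not justify applying thematic coding to graphs.

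The article also states no rating scale and no requirement for daily completion. That the entries have a graded value is inferred from their being plotted.

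**Conclusion.** The point holds as a mismatch between a named secondary outcome and its assigned analysis, together with a schedule mark that cannot be met as described. Followed as written, the plan gives no numerical estimate of change in mood, and one of four scheduled mood and sleep points has no monthly graph behind it.

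The size is limited. No primary objective, power statement or anxiety and depression result is affected. What is lost is a before, during and after comparison of the diary outcomes, covering at most about 28, 180 and 60 days per participant. No bias or loss of power can be calculated from the article.

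The conclusion rests on three assumptions: the diary is not used before enrolment, the plotted entries carry a graded value, and no free-text mood field exists beyond what is described. If such a field does exist, thematic coding would suit that field but still not the plotted entries.

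**What to change.** 1. In the statistical section, take mood out of the thematic list and place mood and sleep diary entries with the numerical data. Keep thematic coding for free text.
2. Summarise entries by period: T1 to T2 as the single baseline block, then the parkrun period, then T3 to T4 as follow-up. Compare the later periods with the baseline block in a repeated-measures model with a participant random intercept, the structure the article already uses for physical activity. State the scale of the entries, and report how many each participant made in each period.
3. In Table 1 and in the mood and sleep paragraph, replace the separate T1 and T2 diary marks with one control-block entry, and define T3 and T4 by the periods above.
4. Ask participants to export entry values and not only graphs.

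The cost is a few lines of text and one table edit, plus a change to the export instruction. The article reports that recruitment is about to start and no data have been collected, so the change can be made before the first diary begins. The downside is participant time for exporting values or, if only graphs can be obtained, staff time for transcribing them.

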## Outcomes

### Study objectives

This feasibility study has been developed primarily to assess the acceptability of, and adherence to, parkrun as an enjoyable exercise intervention for cancer survivors. Secondary aims are to assess the efficacy of parkrun to improve social support, HRQoL, mental health, to prevent physical and functional decline [3, 4, 26] as well as influence dietary intake [26–28]. 

We hypothesised that:

Consistent parkrun participation will improve cancer survivor engagement in physical activity, social interaction and social identity.Cancer survivors will enjoy doing parkrun events.Parkrun participants will have improved physical function, HRQoL, mental health, disease symptoms and treatment side-effects compared to baseline measures.Parkrun participation may indirectly affect the dietary intake of cancer survivors.

Outcome measures will be assessed at enrolment and initial screening [25] (baseline, T1); after 4 weeks of usual management and activities of daily living (ADL, T2); after 6 months of parkrun participation (T3); 2 months post-intervention follow-up (T4) (Fig. 1).

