### Limitations

The study has several strengths and limitations. Advantages include the use of an existing exercise program that has no direct costs, is easily accessible, is outdoors, and is supportive and safe in nature. The study will comprehensively profile participants and will have quantitative and qualitative outcome measures, participants’ experiential data and follow-up surveys. Limitations include the lack of randomisation and inclusion of participants with different types and stages of cancers. However, using a heterogenous sample is useful from the perspective of real-world clinical practice. As a feasibility study, this trial aims to identify benefits and barriers that affect parkrun participation and participant enjoyment and acceptance, and to lead to a larger longitudinal study.

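### Enjoyment and acceptability belong to the primary objective, but the only stated analysis is thematic coding, which does not estimate what share of participants enjoyed or accepted parkrun

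*Protocol article*

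**What the plan says.** Under Study objectives, the protocol article says the study was developed "primarily to assess the acceptability of, and adherence to, parkrun as an enjoyable exercise intervention for cancer survivors". The second hypothesis in the same section reads "Cancer survivors will enjoy doing parkrun events".

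Outcome measures describes the participant survey given at T3 and T4. Its one explicitly closed component is a checklist on eating and exercise behaviours. Enjoyment is gathered elsewhere in it: "The survey also includes a series of open-ended questions about parkrun where participants are encouraged to provide their opinions, likes and dislikes, levels of enjoyment". As examples, "specific questions ask whether participants find parkrun fun and acceptable as rehabilitation exercise; whether it is easy to join in". No response scale or score is given for these questions.

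Under Statistical analyses, sample size and power calculation, scored questionnaires go to numerical analysis. Survey responses and attitudes are classed as qualitative data, and "enjoyment, appropriateness, suitability, convenience and perceived effectiveness of the intervention) will be analysed thematically using NVivo". The coding framework is to be drawn from the data and also "informed by the survey questions and themes highlighted in wider literature on parkrun outcomes".

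Adherence, the other half of the primary objective, is a percentage: events attended divided by events available over the 6 months. Under Limitations, the study is meant, among other aims, "to lead to a larger longitudinal study".

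**The concern.** Hypothesis 2 is a statement about survivors as a group. To judge it, a reader needs to know roughly how many participants enjoyed parkrun, and likewise how many found it acceptable as rehabilitation. Thematic coding answers a different question: which views are present, and what lies behind them. A theme of enjoyment looks much the same on paper whether it comes from a fifth of participants or nine tenths.

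This is a method the article names for part of the primary objective, so it is more than a detail left for later. If the survey asks only open questions, no later analysis text can supply responses to closed items that were never asked. At stake is how firmly the acceptability result can support a larger study.

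**Working it through.** **1. What the plan fixes for each half of the primary objective.**

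| Component | Collected by | Stated analysis | Estimate produced |
|---|---|---|---|
| Adherence | Parkrun barcode records | Attended / available × 100 | Percentage per participant |
| Acceptability, enjoyment | Open-ended questions, T3 and T4 | Thematic coding in NVivo | None stated |

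The article gives no figure for enjoyment or acceptability, so there is nothing of its own to reproduce on this point. Its power statement concerns the proportion meeting physical activity guidelines. The only number borrowed here is the sample after attrition: 100 − 20 = 80.

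**2. How often favourable comments occur when only a minority enjoy parkrun.** Let X be the number of the n = 80 respondents who enjoy parkrun and say so, with true share p. Then X is binomial, and

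P(X ≥ k) = Σ (j = k to 80) C(80, j) p^j (1 − p)^(80 − j).

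Here k is the number of commenters taken to make a theme. The article gives no value, so a range is shown.

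| True share p | Expected 80 × p | k = 5 | k = 10 | k = 20 |
|---|---|---|---|---|
| 10% | 8 | 0.91 | 0.28 | 0.0001 |
| 20% | 16 | 0.9999 | 0.97 | 0.16 |
| 30% | 24 | 1.00 | 0.9999 | 0.86 |

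When 20% or 30% enjoy parkrun, favourable comments reach 5 or 10 people almost always. At 10% the answer depends heavily on k. At p = 20%, 80 − 16 = 64 respondents would be expected not to enjoy it, so an unfavourable theme would be at least as likely to appear. Both themes would then be present, and the method as stated gives no share to weigh one against the other.

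**3. What a closed item would give.** Suppose, purely as an example, that 56 of 80 respondents agree. The exact (Clopper-Pearson) 95% limits for x of n are the 2.5% quantile of Beta(x, n − x + 1) and the 97.5% quantile of Beta(x + 1, n − x).

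- Among respondents: 56/80 = 70%, interval 58.7% to 79.7%.
- Among all enrolled, counting the 20 non-respondents as not agreeing: 56/100 = 56%, interval 45.7% to 65.9%.

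The denominator matters. 50 of 80 respondents is 62.5%, but the same 50 people are 50% of the 100 enrolled.

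**The case against.** The strongest reply is that the analysis can come out unfavourable. The survey asks for dislikes and barriers as well as likes. Participants who miss events or leave are followed up for their reasons. The coding framework is drawn from the data first, with the survey questions and the literature as additional input. Attendance is at participants' discretion and recorded objectively, so poor uptake would be visible evidence against an acceptability claim. All of this stands.

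A reader might therefore be tempted by two stronger claims that the article does not support. One is that thematic coding guarantees a supportive finding, or cannot tell a liked programme from a disliked one. Nothing in the article says a theme counts as support whatever its frequency, and a report dominated by complaints would not read as success. The other is that the framework is tilted towards favourable published themes. The Background does summarise the parkrun literature favourably, but the data-driven part of the framework is explicit and the cited themes are not visible here.

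It can also be said that the survey instrument is not shown, that questions such as "specific questions ask whether participants find parkrun fun and acceptable as rehabilitation exercise" could be tallied, and that Data management mentions quantitative as well as qualitative use of coded data. These leave room for a count. But the questions are introduced as examples of open-ended ones, and the data-management sentence is tied neither to enjoyment nor to any summary.

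**Conclusion.** The point holds in a limited form. As written, the plan yields no estimate of the share of participants who enjoyed parkrun or found it acceptable, although both belong to the primary objective and enjoyment is the subject of hypothesis 2. A supportive theme can therefore be reported when only a minority enjoyed it. With 80 respondents and a true share of 20%, the chance of enough favourable commenters runs from above 99.9% (5 needed) through 97% (10) to 16% (20).

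These figures rest on an assumed number of commenters per theme and on everyone who enjoyed parkrun saying so. They illustrate the gap and do not measure an error rate of the plan. Adherence is not affected. The matter is worth correcting because the remedy is cheap and has to be in the survey before it is given.

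**What to change.** Before the first T3 survey:

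- Ask the questions on whether parkrun is fun and whether it is acceptable as rehabilitation exercise as fixed-response items, for example on a 5-point agreement scale. Keep the open questions alongside.
- Under Statistical analyses, state that the proportion agreeing with each item will be reported with an exact 95% confidence interval, both among respondents and among all enrolled, with non-respondents counted as not agreeing.
- Have the investigators fix in advance the proportion they would regard as supporting hypothesis 2. The choice of bar is theirs.
- State that the thematic analysis explains why participants did or did not enjoy parkrun, and that the proportions address whether they did.

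The cost is a slightly longer survey and a few sentences of analysis text, with no extra visits or participants. The ethics committee and the parkrun Research Board have already approved the study, so a minor ethics amendment may be needed. The acceptability claim can also then come out negative against a stated bar. The article reports that recruitment was about to start and no data had been collected. T3 follows 4 weeks of usual activity and 6 months of parkrun, so at that stage there was time to make the change.

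### The plan fits a normal-error linear mixed model to a yes/no outcome, so its residual check cannot be met, and it leaves the inferential model to be chosen from the data; the time test itself is little affected

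*Protocol article*

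**What the plan says.** All of this is in the protocol article under Statistical analyses, sample size and power calculation.

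- Model and target: "Linear mixed effect models will be used to determine the effect of parkrun participation on the proportion of participants meeting minimal PA recommendations".
- Level of analysis: "These models will include a random intercept for each participant, to account for the clustering of observation on each individual". The visits are listed as "measurements at baseline, 4-weeks usual activities, following 6 months of parkrun participation, and 2-month follow-up", so there are four.
- Diagnostic: "A histogram and quantile-quantile plot of the model residuals will be used to determine whether the assumption of normally distributed errors is met".
- Choice of model: fit is judged by adjusted R² and residual error, after which "the most parsimonious model will be selected for inferences".
- Standardised summary: "Effect sizes (Cohen’s d) will be calculated where there are significant effects of time using the pooled standard deviation as the denominator".

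The sample-size paragraph of the same section powers the study on the same quantity, "measured as the proportion of cancer patients meeting minimum physical activity guidelines". Its model contains time, BMI and sex as fixed factors and a random intercept per participant. It assumes a 30% baseline proportion and a 30% increase. The analysis paragraph does not carry BMI and sex forward, and no logit link or other binary model is named anywhere.

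**The concern.** A proportion has no participant-level value other than yes or no. The only general physical-activity instrument in Table 1, the IPAQ-SF, is given once at each of T1 to T4, so there is no within-visit proportion that could be treated as continuous. A model with a participant intercept must therefore be fitted to 0/1 responses. The variance of such responses depends on their mean, and their residuals fall in two bands.

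Three things follow. The normality check is one that the stated model cannot pass, so an analyst following the plan must either disregard it or change method with the results in view. The terms of the inferential model are open until the data are seen, even though the sizing paragraph gave reasons for including sex and BMI. And Cohen's d is a poor summary of a change in a proportion. This is the only quantitative inferential model that the article names, and its target is the outcome the study is sized on.

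**Working it through.** **The plan's own figure.** The article gives about 80% power with 80 participants for a 30% increase. For two proportions, power = Φ[(|p2 − p1|√n − 1.96√(2p̄(1 − p̄))) / √(p1(1 − p1) + p2(1 − p2))], two-sided 5%.

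- 30% to 60% (absolute), n = 80, p̄ = 0.45: (0.30 × 8.944 − 1.96 × 0.7036)/0.6708 = 1.944, power 97.4%.
- 30% to 39% (relative), p̄ = 0.345: (0.09 × 8.944 − 1.96 × 0.6723)/0.6693 = −0.766, power 22.2%.

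Neither reading gives 80%. The scale, residual variance and test used in the article's simulation are not stated. That mismatch is a separate matter and nothing below depends on it; both readings are carried forward.

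**Residuals.** If the fitted value is m, the residual is either 1 − m or −m: 0.7 or −0.3 at m = 0.30, and 0.4 or −0.6 at m = 0.60. The participant intercept moves these values but does not fill the gap with a bell shape. Balanced 0/1 data were simulated for 80 participants at three or four visits, with a random-intercept SD of 2% on the probability scale or 0.02 to 3 on the logit scale. The Shapiro-Wilk test, standing in for the histogram and Q-Q plot, rejected normality in 99.6–100% of 500 trials per scenario.

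**Standard errors by visit.** The variance p(1 − p) is 0.21 at 30% and 0.24 at 60%, mean 0.225. √(0.21/0.225) = 0.966 and √(0.24/0.225) = 1.033, so one common variance misstates visit-specific standard errors by about 3%. At 39% the variance is 0.2379 and the mean 0.22395; the ratios are 0.968 and 1.031, again about 3%.

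**Standard error of the time contrast.** With proportions of 30, 30, 60 and 60% and visits treated as independent, the pooled variance is (0.21 + 0.21 + 0.24 + 0.24)/4 = 0.225. The model-based value is √(2 × 0.225/80) = 0.075. The correct value is √((0.21 + 0.24)/80) = 0.075. They agree.

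**Behaviour of the time test, complete data, 80 participants.**

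| Quantity | Linear mixed model (4,000 runs) | Logistic GEE (300 runs) |
|---|---|---|
| Power, 30% to 60% | 97.5% | about 97% |
| Power, 30% to 39% | 23.0% | 22% |
| Type I error, four visits | 4.1–5.1% | 6% |

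The power rows use an intercept SD of 2%. The linear type I range covers the overall and the contrast test over logit-scale SDs of 0.02 to 3; the GEE type I run used an SD of 2% only. With 300 runs the Monte Carlo standard error at 5% is √(0.05 × 0.95/300) = 1.3 points, so 6% does not differ detectably from 5%.

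**Selection over sex and BMI.** Sex and BMI recorded at T1 do not vary within a person. In a linear random-intercept model with complete data, keeping or dropping them leaves the time contrast unchanged. Across all four sex/BMI subsets in 250 null runs, estimates differed by less than 1e-14. With 100 participants and 20% dropout before T3, estimates differed by at most 0.007 and standard errors by at most 0.6%. No run changed significance in either setting.

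**Cohen's d.** With a pooled SD, d = 0.30/√0.225 = 0.63 for 30% to 60%, and 0.09/√0.22395 = 0.19 for 30% to 39%. The SD is fixed by the proportions themselves, so d re-expresses the risk difference on a less readable scale.

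**The case against.** The strongest reply is that a linear model on 0/1 data is a legitimate linear probability model. It estimates the risk difference directly, and the results above show no loss of error control and no gain in power from a logistic GEE. That stands, and it limits the point. But a deliberate linear probability model would use robust standard errors and would not be judged by normal residuals; the article does the opposite.

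A reader might infer more than the documents support:

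- *That the p-value for time would be materially wrong.* The simulations do not show this.
- *That standard errors are off by 10–15%.* This needs about 80% of participants meeting the guideline: √(0.16/0.21) = 0.87. The article gives no such rate; its own figures lead to about 3%.
- *That model selection inflates the error rate.* Over the only covariates the article names, it did not. No candidate set is listed, so other forms of selection, for example of the time structure, are neither stated nor excluded.
- *That fitted proportions leave the 0–1 range.* With time as a factor and complete data, the marginal fitted values are the observed visit proportions. Only individual predictions could stray, and the plan does not use them.
- *That the lack of a fallback is itself an error.* A fallback may be left to a fuller plan. The fault is that the article states a check its model cannot meet.

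Mixed-model analogues of adjusted R² exist, so that term is loose rather than demonstrably wrong. The stated primary objectives, acceptability and parkrun adherence, do not rest on this model, and no decision rule hangs on it in this single-arm feasibility study.

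**Conclusion.** The point holds in limited form. The article fixes a normal-error model and a normality check for a yes/no outcome, and the check will fail in practically every possible dataset. It also leaves the inferential model open until the data are seen, although time, sex and BMI had been settled for sizing, and it summarises a proportion by Cohen's d. The cost is to coherence and pre-specification. The test of time stays near 5% type I error, and visit-specific standard errors are off by about 3%. It should be fixed, but it does not threaten the study's conclusions by itself.

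This rests on one yes/no classification per person per visit, which is inferred from the participant intercept and the IPAQ-SF schedule. It also rests on a 30% baseline rising to 39% or 60%. The type I and power results are for complete data, and the comparison with a logistic GEE was run only at an intercept SD of 2%.

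**What to change.** For the proportion meeting PA recommendations, pre-specify a mixed-effects logistic model or a binomial GEE with robust standard errors, with time as a four-level factor plus sex and baseline BMI, and name the time contrast of main interest. Report the proportion at each visit and risk differences with 95% confidence intervals in place of Cohen's d. Delete the normal-residual check, the adjusted R² and residual-error criteria, and the rule that "the most parsimonious model will be selected for inferences" for this outcome. Keep linear mixed models with residual plots for the continuous scores, such as the 6MWT, sit-to-stand, EORTC QLQ and HADS. A deliberate linear probability model with robust standard errors and the same fixed terms would also be acceptable.

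The cost is a few sentences. R and SPSS, both already named, can fit these models. The article says that no data had been collected, so at that stage the change could be made without knowledge of results.
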